## Abstract

**Background:**

There is currently no validated strategy for the timing of renal replacement therapy (RRT) for acute kidney injury (AKI) in the intensive care unit (ICU) when short-term life-threatening metabolic abnormalities are absent. No adequately powered prospective randomized study has addressed this issue to date. As a result, significant practice heterogeneity exists and may expose patients to either unnecessary hazardous procedures or undue delay in RRT.

**Methods/design:**

This is a multicenter, prospective, randomized, open-label parallel-group clinical trial that compares the effect of two RRT initiation strategies on overall survival of critically ill patients receiving intravenous catecholamines or invasive mechanical ventilation and presenting with AKI classification stage 3 (KDIGO 2012). In the ‘early’ strategy, RRT is initiated immediately. In the ‘delayed’ strategy, clinical and metabolic conditions are closely monitored and RRT is initiated only when one or more events (severity criteria) occur, including: oliguria or anuria for more than 72 hours after randomization, serum urea concentration >40 mmol/l, serum potassium concentration >6 mmol/l, serum potassium concentration >5.5 mmol/l persisting despite medical treatment, arterial blood pH <7.15 in a context of pure metabolic acidosis (PaCO_2_ < 35 mmHg) or in a context of mixed acidosis with a PaCO_2_ ≥ 50 mmHg without possibility of increasing alveolar ventilation, acute pulmonary edema due to fluid overload despite diuretic therapy leading to severe hypoxemia requiring oxygen flow rate >5 l/min to maintain SpO_2_ > 95% or FiO_2_ > 50% under invasive or noninvasive mechanical ventilation.

The primary outcome measure is overall survival, measured from randomization (D0) until death, regardless of the cause. The minimum follow-up duration for each patient will be 60 days. Two interim analyses are planned, blinded to group allocation. It is expected that there will be 620 subjects in all.

**Discussion:**

The AKIKI study will be one of the very few large randomized controlled trials evaluating mortality according to the timing of RRT in critically ill patients with AKI classification stage 3 (KDIGO 2012). Results should help clinicians decide when to initiate RRT.

**Trial registration:**

ClinicalTrials.gov NCT01932190.

## Background

Acute kidney injury (AKI) is common in intensive care unit (ICU) patients [1-3]. Despite progress in symptomatic management of AKI and technical advances in renal replacement therapy (RRT) techniques [4], mortality remains very high (50 to 60%) [5].

Life-threatening metabolic complications, such as severe hyperkalemia or overload pulmonary edema responsible for refractory hypoxemia, are accepted indications for RRT during AKI [6,7]. In contrast, the accumulation of uremic or other putative toxins has not been shown to be a risk factor *per se* for mortality in AKI and cannot be used as a reliable indication for RRT. Similarly, severe gastrointestinal bleeding, a classical complication of AKI, has almost disappeared during AKI for multiple reasons (better management of infection and shock, prophylaxis with inhibitors of gastric acid secretion) [8,9].

Although many authors and experts favor early RRT [10-12], some hypothesized that too early an RRT initiation might be harmful [13,14]. Several studies have recently suggested that delaying or even avoiding RRT could benefit patients with AKI [15,16]. These uncertainties result in significant practice heterogeneity [17], making a randomized controlled trial on the timing of RRT initiation not only ethically justified but also desired by many clinicians.

To the best of our knowledge, only one such large randomized controlled study is ongoing [18], while another is due to start in the near future [19].

The Artificial Kidney Initiation in Kidney Injury (AKIKI) trial is a multicenter randomized controlled trial comparing the effects of an ‘early’ RRT initiation strategy with a ‘delayed’ strategy on overall survival of critically ill patients (invasive mechanical ventilation or catecholamine infusion).

## Methods/design

### Design and settings

The AKIKI study is a prospective, multicenter, open-label, two-arm randomized study. This study is conducted of patients receiving invasive mechanical ventilation or catecholamine infusion who have AKI classification stage 3 (KDIGO 2012) [20]. An ‘early’ strategy where RRT is initiated immediately after randomization will be compared with a ‘delayed’ strategy, where RRT is initiated only if one or more ‘severity’ (potentially life-threatening complications of AKI) criteria occur. These criteria are:Oliguria or anuria for more than 72 hours after randomization,Serum urea concentration >40 mmol/l,Serum potassium concentration >6 mmol/l,Serum potassium concentration >5.5 mmol/l persisting despite medical treatment (bicarbonate or glucose-insulin infusion),pH <7.15 in a context of pure metabolic acidosis (PaCO_2_ < 35 mmHg) or in a context of mixed acidosis with PaCO_2_ ≥ 50 mmHg without possibility of increasing alveolar ventilation,Acute pulmonary edema due to fluid overload leading to severe hypoxemia requiring oxygen flow rate >5 l/min to maintain SpO_2_ > 95% or FiO_2_ > 50% in patients already undergoing invasive or noninvasive mechanical ventilation and despite diuretic therapy.

Patients have to be adequately resuscitated (fluid and or catecholamine infusion) before potential inclusion; this is to avoid enrolling patients with rapidly reversible renal failure and to allow clinician to diagnose acute tubular necrosis with reasonable accuracy.

### Ethical aspects

The study protocol and information forms were approved by the ethical committee of the French Society of Intensive Care Medicine (Société de Réanimation de Langue Française, approval number CE SRLF 13–005) and by the competent French legal authority (*Comité de Protection des Personnes d’Ile de France VI, Groupe Hospitalier Pitié Salpêtrière*; registration number: 2013-A00765-40; date of approval 29 May 2013).

Patients are informed orally and provided with a written document about the AKIKI study by the investigators. By French law, written informed consent is not required, as the standard of care encompasses both study interventions. As already mentioned, patients or surrogates are informed about the trial and their right to refuse participation. If the patient is unable to receive appropriate information, decision is made by a substitute decision maker. Patients who are eligible but incapable of receiving information and for whom a substitute decision maker is not available may be randomized through a process of deferred information. They are informed about participation as soon as their clinical status allows.

### Participating intensive care units

A total of 31 French ICUs are participating in the study. All study sites have medical and paramedical teams who are experienced in the field of RRT. Because data in the literature fail to suggest a conclusion on a definite benefit of one RRT modality over another (intermittent hemodialysis or continuous techniques), the choice of RRT modality is left to the team’s discretion depending on their usual practice. In each study site, RRT prescription and monitoring are standardized according to the French national guidelines from panel experts [21].

### Study population

Eligible patients are adults (≥18 years) hospitalized in study ICUs with AKI compatible with the diagnosis of acute tubular necrosis in a context of ischemic or toxic aggression and receiving invasive mechanical ventilation or catecholamine infusion. To be randomized, patients must fulfill at least one of the three following criteria: serum creatinine concentration > 354 μmol/l or greater than three times the baseline creatinine level, anuria (urine output <100 ml) for more than 12 hours, oliguria (urine output <0.3 ml/kg/h or <500 ml/day) for more than 24 hours. These three criteria represent stage 3 of the KDIGO classification [20].

### Randomization

Eligible patients are consecutively randomly allocated to one of the two study treatment arms, termed ‘early’ and ‘delayed’ RRT strategies. Randomization and concealment are achieved using a centralized, secure, computer-generated, interactive, web-response system accessible from each study center. The randomization is balanced by blocks of variable and undisclosed size and stratified on the center. Before randomization, the presence of the inclusion criteria and the absence of the non-inclusion criteria are verified. The randomization day is the study day zero (D0).

### Study interventions

The study protocol and both arms of randomization are detailed in Figure 1.

**Figure 1 Fig1:**
[figure not shown]
Flow chart of the trial. AKI, Acute kidney injury; D60, day 60; KDIGO, kidney disease: improving global outcome; RRT, renal replacement therapy.

When indicated (allocation to early RRT strategy or occurrence of at least one severity criterion in patients allocated to delayed RRT strategy), RRT is initiated as quickly as possible.

As already explained, the choice of RRT modality is left to the study site’s discretion. Several RRT modalities can be used in the same patient, according to the attending physician’s indication. The duration of and interval between sessions, and device settings and modality of anticoagulation are left to the investigator’s discretion.

Clinical and biological parameters are monitored, to detect and treat any complication directly (hyperkalemia, metabolic acidosis, pulmonary edema) or indirectly (bleeding, infection, thrombosis…) related to AKI or RRT.

#### ‘Early’ RRT strategy

Renal replacement therapy is initiated within 6 hours after documentation of AKI stage 3 of KDIGO classification. The timing of the initiation is recorded and RRT is continued until criteria for cessation are observed.

#### ‘Delayed’ RRT strategy

Renal replacement therapy is initiated only if one or more of the severity criteria occur. When required, RRT is performed with the same modalities and stopped according to the same criteria as for the ‘early’ RRT strategy.

#### Criteria for RRT cessation

Discontinuation of RRT is contemplated if spontaneous diuresis is ≥500 ml per 24 h, and highly recommended if diuresis is >1000 ml per 24 h without diuretic administration or ≥2000 ml/24 h in patients receiving diuretics.

Cessation of RRT is mandatory if diuresis is present and serum creatinine level decreases spontaneously.

#### Criteria for RRT resumption

In the absence of sufficient renal function recovery to achieve a spontaneous decrease in creatinine level or of a diuresis greater than 1000 ml/24 h without diuretics (or greater than 2000 m l/24 h under diuretics), RRT is resumed.

### Authorized treatments (whatever the arm randomization)

#### Pharmacological prevention of gastrointestinal bleeding

Given the risk factors for digestive bleeding in this population (mechanical ventilation or catecholamine infusion in patients with severe AKI), and in the absence of consensus on this issue in available guidelines, the protocol recommends the use of a proton pump inhibitor.

#### Use of diuretics

Diuretics should only be used for the treatment of obvious sodium and fluid overload in patients whose diuresis is ≤500 ml per 24 h.

Use of sodium polystyrene sulfonate and isotonic sodium bicarbonate administration will be left to the clinician’s discretion.

Fluid therapy, including red blood cell transfusion, is left to the investigator’s discretion.

The use of hydroxyethyl starch solutions is discouraged.

### Data collection and follow-up

#### At day zero (D0)

Demographic data and medical history, including the current clinical history with the reason for ICU admission, Simplified Acute Physiology Score III and Sequential Organ Failure Assessment score will be collected. Potential exposure to nephrotoxic agents (for example, aminoglycosides or contrast agents) will be documented. Details of treatments including mechanical ventilation (and its settings), fluid therapy, catecholamine and anticoagulant administration are recorded.

Laboratory tests include determination of serum (and urine if diuresis is present) electrolyte levels, serum glucose level, urea and creatinine concentration, arterial blood gas content, and liver and muscle enzyme concentrations. No renal failure marker identification (such as neutrophil gelatinase-associated lipocalin) is planned because the clinical usefulness of these markers in routine care has not yet been demonstrated [19].

Baseline (that is, before occurrence of AKI) serum creatinine concentration will be recorded. Baseline serum creatinine concentration will be determined from either the results of a measurement in the 12 months preceding the ICU stay or estimated using the Modification of Diet in Renal Disease Study Group formula [22]. As a special case, if serum creatinine concentration was measured more than 12 months before admission, the baseline level will be considered as the higher of the two estimates (former serum concentration or that computed using the Modification of Diet in Renal Disease formula).

#### From D1 to D28

The same biological data as collected at inclusion will be recorded according to clinical indication for routine care until discharge from the ICU, day 28 in the ICU, or death in the ICU. A search for infection (including catheter-related infection) or complications related to RRT or AKI will be carried out according to routine care procedures. The Sequential Organ Failure Assessment score will also be calculated at D3, D7, D14, D21, and D28.

#### At D60

Vital status (alive or dead) and duration of hospital and ICU stay will be recorded. Details and timings of patient follow-up are summarized in Table 1.

**Table 1 Tab1:** **Flowchart of patient follow-up**

	**D0 inclusion**	**Daily from D1 to D28**	**D28**	**D60**
Inclusion and exclusion criteria	**X**			
Demographic data and history	**X**			
Clinical assessment	**X**	**X**		
Laboratory tests	**X**	**X**		
Baseline creatininemia	**X**			
Simplified Acute Physiology Score III	**X**			
Sequential Organ Failure Assessment	**X**	D3, D7, D14, D21, D28		
Mechanical ventilation	**X**	**X**		
Treatment with catecholamines	**X**	**X**		
Renal replacement therapy initiation	**X**	**X**		
Renal replacement therapy technique used	**X**	**X**		
Complications of renal replacement therapy or acute kidney injury		**X**		
Total cost of renal replacement therapy				**X**
Duration of stay in intensive care unit or hospital			**X**	**X**
Alive or dead status			**X**	**X**

#### After D60

Vital status and dialysis dependency will regularly be updated for each patient until the end of the study (that is, day 60 after inclusion of the last patient).

#### Coordination and implementation of the trial

Each medical and paramedical team in the 31 participating ICUs were trained in the protocol and data collection using an electronic case-record form during formal meetings prior to screening and inclusion. The electronic case-record form was developed with CleanWEB^TM^, a centralized, secure, interactive, web-response system accessible from each study center, provided and managed by Telemedicine Technologies.

Local physicians and clinical research assistants in each participating ICU are responsible for daily screening and inclusion of patients, compliance with protocol, availability of data requested for the trial and completion of the electronic case-record form. In accordance with French law, the electronic case-record form and database were validated by appropriate committees (Comité Consultatif sur le Traitement de l’Information en matière de Recherche dans le domaine de la Santé; Commission Nationale de l’Informatique et des Libertés).

#### Interim analysis

Two interim analyses by an independent data safety and monitoring board are planned after the occurrence of 90 and 180 deaths. The data safety and monitoring board will be blinded to allocation of groups and may decide premature termination of the study. The board consists of one methodologist, one nephrologist, and two intensivists. Data are blindly analyzed but unblinding is possible on request of the data safety and monitoring board. An extraordinary meeting may be requested by the principal investigator or the methodologist, in the case of unexpected events that might affect continuation of the protocol.

### Blinding

Given the nature of the interventions, physicians, nurses, and patients cannot be blinded for the randomized interventions. Lack of blinding is, however, partially counter-balanced by the objective nature of the primary outcome measure [23]. The analysis will be blinded to allocation of groups.

### Study outcomes

#### Primary endpoint

The primary endpoint measure is the overall survival. Overall survival is measured from the randomization date (D0) until death, regardless of the cause. For patients discharged alive, information on the primary endpoint measure will be collected by a telephone call to the patient’s home or by a conversation with the physician in charge, if the patient is still in a care facility. The minimum follow-up duration for each patient will be 60 days. The status (alive or dead) of patients lost to follow-up before the planned follow-up duration will be checked by obtaining their birth certificate (eventual demise is indicated in this official document) from the City Hall of their city of birth (French law allows anyone to ask for such certificate). Patients for whom vital status remains unknown at D60 (a rare occurrence) or who are still alive at the end of their follow-up period will be censored at the last date to which their health status has been documented.

#### Secondary endpoints

Secondary endpoint measures are the percentage of patients receiving RRT at least once in the ‘delayed’ RRT strategy arm (compared with the 100% of patients in the ‘early’ strategy); the number of RRT sessions per patient (analyzing living and dead patients separately); the time between randomization (D0) and RRT initiation; the time between observation of at least one of the severity criteria (which mandates RRT in the delayed strategy) and RRT; the time to RRT weaning; the number of days alive without RRT (between D0 and up to D28); the time between D0 and the first RRT and between the last RRT and D60; the number of dialysis catheter-free days between D0 and D28; the rate of adverse events potentially related to AKI or RRT (including: (a) hemorrhage requiring red blood cell transfusion or surgical procedure, (b) thrombocytopenia (<100,000 platelets/mm^3^), (c) thrombosis of a large venous axis diagnosed by Doppler ultrasonography, (d) hypokalemia (defined as serum potassium concentration < 3 mmol/l), (e) hypophosphatemia (defined as a serum phosphate concentration < 0.6 mmol/l), (f) hyperkalemia (>6.5 mmol/l), (g) cardiac rhythm disorders (ventricular tachycardia, ventricular fibrillation, torsades de pointes or a new episode of atrial fibrillation requiring medical treatment or external electric counter shock); the number of days alive without mechanical ventilation between D0 and D28; the rate of nosocomial infections (bloodstream, lung and catheters and unexplained bacteremia or fungemia); the number of days alive without vasopressors between D0 and D28; the progression of organ failures assessed using the Sequential Organ Failure Assessment score; the duration of stay in the ICU and in hospital generally (limited to D60); the survival rate at D28; the proportion of patients with treatment limitations (withholding or withdrawal); and the total cost of RRT-related consumables between D0 and D28 (catheters, solutions for RRT, membranes, and circuitry).

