#### Other analyses

Categorical variables will be compared using the χ^2^ or Fisher’s test, as appropriate. Continuous variables will be compared using Student’s *t* test or the Wilcoxon test, as appropriate.

The analysis of the overall survival will be adjusted for important stratification and prognostic factors using a multivariate analysis (Cox model). The adjustment factors will include: baseline Simplified Acute Physiology Score III, RRT technique used, treatment with catecholamines at baseline, mechanical ventilation at baseline, septic shock at baseline, time between admission in ICU and AKI development (less than, greater than, or equal to 7 days).

All secondary analyses will be conducted at the bilateral alpha risk of 5%.

Analyses will be performed using R software (R Foundation for Statistical Computing, Vienna, Austria) version 2.14 or later, or SAS version 9.2.

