We hypothesize that patients in the delayed RRT strategy arm may have a chance of recovering acceptable renal function, obviating the need for RRT and that the others may have RRT performed in better conditions.

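### Analysing RRT sessions separately in living and dead patients conditions on the primary outcome, so if mortality differs each subset can show a between-arm difference that is not an effect on sessions

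*Protocol article*

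**What the plan says.** The list of secondary endpoints in the protocol article includes "the number of RRT sessions per patient (analyzing living and dead patients separately". The same list contains "the time between randomization (D0) and RRT initiation", "the time to RRT weaning" and "the duration of stay in the ICU and in hospital generally (limited to D60". It also contains endpoints that take account of death, among them days alive without RRT from D0 to D28.

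The section Other analyses gives one general rule for continuous data: "Continuous variables will be compared using" Student's t "test or the Wilcoxon test, as appropriate". It sets two-sided 5% for all secondary analyses. Kaplan-Meier, log-rank and Cox methods are named only for overall survival.

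Receipt of RRT is expected to differ between arms. The delayed arm's percentage is to be "compared with the 100% of patients in the ‘early’ strategy", and the Discussion expects that some delayed-arm patients "may have a chance of recovering acceptable renal function, obviating the need for RRT".

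**The concern.** Randomization makes the two arms comparable as a whole. It does not make the early-arm survivors comparable with the delayed-arm survivors, because survival is an outcome the strategy is meant to change.

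Suppose delayed RRT saves lives as hypothesised. Its survivors then include sicker patients who would have died under early RRT, and its non-survivors are a sicker remainder. If sicker patients also need more sessions, the delayed arm shows more sessions in both subsets even though the strategy left sessions unchanged.

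What is at stake is the reading of RRT burden, one of the reasons to prefer a delayed strategy. A significant result in one subset, or in both, could be reported as an effect on sessions when it only reflects who survived.

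**Working it through.** **Inputs from the protocol article.** Mortality 55% early and 41% delayed, 90% power, two-sided 5% (Sample size calculation); 263 deaths and 546 subjects for a single analysis (Table 2); 620 planned, taken as 310 per arm (Total planned sample size); two-sided 5% for secondary analyses (Other analyses).

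**The plan's own figure.** Freedman's formula with hazard ratio 1.5 gives (1.960 + 1.282)² × [(1 + 1.5)/(1 − 1.5)]² = 10.507 × 25 = 262.7, so 263 deaths, as stated. Mean mortality is (0.55 + 0.41)/2 = 0.48, and 263/0.48 = 548 subjects against the stated 546. The figure is reproduced, so 55% against 41% is a fair working scenario.

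**Size of the subsets under that scenario.** Survivors: 310 × 0.45 = 140 early and 310 × 0.59 = 183 delayed. Non-survivors: 310 × 0.55 = 171 early and 310 × 0.41 = 127 delayed.

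**How equal totals can hide unequal subsets.** In one simulated illustration, with sessions depending on severity only and no effect of arm, the means were:

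| | Early | Delayed | Ratio |
|---|---|---|---|
| Survivors | 3.27 | 3.43 | 1.05 |
| Non-survivors | 4.56 | 4.78 | 1.05 |
| All patients | 3.98 | 3.98 | 1.00 |

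The rows agree: 0.45 × 3.27 + 0.55 × 4.56 = 3.98, and 0.59 × 3.43 + 0.41 × 4.78 = 3.98. Both subsets show a false 5% excess for the delayed arm.

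**False-positive rates.** Assumed model: severity U is standard normal, sessions are Poisson with mean exp(1.2 + 0.6U) in both arms, and death occurs when a variable correlated with U exceeds the cut that gives the arm's mortality. There were 310 patients per arm, 2000 replicates and a Wilcoxon test at 5%. Mean differences are delayed minus early.

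| Severity-death correlation | All randomized | Living (mean difference) | Dead (mean difference) |
|---|---|---|---|
| 0 | 5.4% | 4.3% (0.01) | 5.0% (0.01) |
| 0.3 | 5.6% | 6.6% (0.15) | 6.7% (0.17) |
| 0.5 | 4.8% | 10.9% (0.22) | 11.6% (0.33) |
| 0.7 | 5.6% | 18.2% (0.27) | 22.3% (0.48) |

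With 55% mortality in both arms and the same death mechanism, the subset tests rejected 4.0 to 6.2% of the time. Repeating the runs with another seed moves individual entries by one or two percentage points and leaves the pattern unchanged.

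**An all-patient session count is not a clean substitute.** The model above does not let death stop the sessions. Assume instead 0.4 sessions per day until recovery, death or D28, mean recovery of 10, 15 or 25 days, no link with severity, and the same 55% against 41% mortality. The all-patient comparison then rejected in 6%, 10% and 12% of runs, with a spurious gap of 4 to 5%. The survivor comparison stayed at 5%, and the non-survivor comparison at 5 to 6%.

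**Weaning, if tested in RRT recipients only.** Assumed: all early-arm patients receive RRT, weaning time depends on severity, and there is no effect of arm. With 80%, 65% or 50% of the delayed arm receiving RRT, a Wilcoxon test rejected in 16%, 30% and 46% of runs at a severity-receipt correlation of 0.3, and in 33%, 66% and 86% at 0.5. At zero correlation the rate was about 5%.

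**The case against.** Four arguments can be made for the plan.

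- **The split has a reason.** Sessions stop at death, so a raw count in everyone flatters the arm with more deaths. The truncation runs confirm this. The argument stands against replacing the split by an unqualified all-patient count. It does not make the subsets randomized groups, and which approach misleads more depends on how strongly severity drives death and sessions.
- **The split may be descriptive.** No test is named for it. That is possible, but nothing in the text says so, and all secondary analyses are placed at two-sided 5%.
- **Days alive without RRT is already listed.** This is true and makes the fix cheap. The article does not say which measure carries the RRT-burden conclusion.
- **The bias is small and runs against the delayed arm.** In these models the false excess is 0.15 to 0.48 sessions and disfavours the strategy the investigators expect to be better. It would not create support for their hypothesis, but it could hide or distort a true difference in burden.

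A reader might infer more than the document supports:

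- **t or Wilcoxon tests on the durations.** The general rule is assigned to no named endpoint and is qualified by "test or the Wilcoxon test, as appropriate". An analysis plan not shown here may use time-to-event methods. The point on weaning is therefore conditional.
- **False differences in time to RRT.** This interval differs by design, so a difference there is real.
- **Length of stay conditioning on survival.** The article does not restrict stay to survivors. With the same discharge process and 55% against 41% mortality, simulated stay to D60 was about 1.3 days shorter in the arm with more deaths (21% rejection). That is a true difference in bed-days caused by death and calls only for careful reading.

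**Conclusion.** The point holds for the sessions endpoint. The article fixes an analysis within groups defined by the primary outcome, and under the trial's own hypothesis this gives up the protection of randomization.

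The false-positive rate is roughly 6 to 22% against a nominal 5%, for assumed severity-death correlations of 0.3 to 0.7. Two conditions are needed: mortality must differ between arms, and severity must drive both death and sessions. The correlations and the session model are assumptions; the article gives no data on them. There is no inflation at zero correlation, nor with equal mortality and the same death mechanism.

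For weaning, the warning applies only if the arms are compared among RRT recipients. The primary analysis is untouched.

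**What to change.** 1. Label the split of sessions by vital status as descriptive, without a between-arm test, and state the day at which living or dead is fixed. This matters because vital status continues to be updated after D60 until the study ends.
2. State that the between-arm conclusion on RRT burden rests on days alive without RRT from D0 to D28 in all randomized patients. Because this measure mixes mortality with RRT use, report it beside both components.
3. If sessions are also shown for all randomized patients, count zero for those never given RRT and note that death truncates the count.
4. If time to weaning is compared between arms, treat death as a competing event and do not apply t or Wilcoxon tests to RRT recipients only, because receipt differs by arm and depends on prognosis.
5. Report length of stay with the caveat that death shortens it.

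The cost is a few sentences of wording and slightly more analysis work. No new data are needed, and the sample size and primary analysis do not change.

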### Statistical methods

#### Sample size calculation

The aim of this study is to demonstrate a difference in outcome between two therapeutic strategies. Our primary hypothesis is that the ‘delayed’ RRT strategy might be beneficial to patients with AKI. The sample size calculation is based on the primary endpoint measure: overall survival.

The expected mortality of patients included in this type of studies may be estimated at around 55%, according to the literature [2,24-26]. Indirect evidence from retrospective studies [13,16] suggests that a 15% decrease in mortality can be expected with delayed indication for RRT (the reasons for this are explained in the discussion section).

To demonstrate a 14% decrease in mortality (from 55 to 41%, corresponding to a relative reduction in the risk of mortality by 1.5 in the ‘delayed’ RRT strategy arm, assuming exponential survival), a total of 546 subjects (273 per group) should be randomized to provide a study power of 90%, with an alpha risk of 5% between both treatments (bilateral formulation).

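### Dialysis catheter-free days and the interval from last RRT to D60 carry no alive condition, so a literal count credits time after death and shifts the arm contrast towards the higher-mortality arm

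*Protocol article*

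**What the plan says.** All the definitions at issue stand in one list, in the protocol article under Secondary endpoints.

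Three endpoints build survival into the count:
- "the number of days alive without RRT (between D0 and up to D28"
- "the number of days alive without mechanical ventilation between D0 and D28"
- "the number of days alive without vasopressors between D0 and D28"

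A fourth keeps survivors and deaths apart: "the number of RRT sessions per patient (analyzing living and dead patients separately".

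Two endpoints do neither:
- "the number of dialysis catheter-free days between D0 and D28"
- "the time between D0 and the first RRT and between the last RRT and D60". The second part of this item ends at a fixed calendar day.

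Under Other analyses, continuous variables go to a t test or a Wilcoxon test, and no rule for death is given. Under Sample size calculation, mortality is planned to fall "from 55 to 41%, corresponding to a relative reduction in the risk of mortality by 1.5", with exponential survival and no stated time horizon.

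**The concern.** Death was dealt with in four items of the list and not in these two. An analyst who follows the words would treat death differently for endpoints meant to be read together.

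The effect on single patients is large. A patient who dies on D2 with a catheter in place would get about 28 − 2 = 26 catheter-free days. A patient whose last RRT was on D2 and who dies on D3 would get 60 − 2 = 58 days. Very early death then yields high values on both.

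The plan expects roughly half the patients to die and expects the arms to differ in mortality. Post-death time would therefore be a large part of both scores and unequal between arms. If the delayed strategy lowers mortality, part of its advantage in catheter-free time is hidden. If it raises mortality, the same mechanism flatters it on an endpoint where it is already expected to use fewer catheters.

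**Working it through.** **Inputs.** Mortality of 55% and 41%, ratio 1.5, 90% power, two-sided 5% and exponential survival come from Sample size calculation. Follow-up of at least 60 days comes from Primary endpoint. The article does not date the mortalities; I assume they apply at D60. It gives no catheter durations; I assume 7 days and show 5 to 21.

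**The plan's own figure.** With h = 1/1.5, Freedman's formula gives (1.960 + 1.282)² × ((1 + h)/(1 − h))² = 10.507 × 25 = 262.7, so 263 deaths, as in Table 2. Dividing by the mean mortality of 0.48 gives 548 subjects against the stated 546. Nothing here disputes that calculation.

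**Step 1: post-death time inside each window.** With F(t) = 1 − exp(−H·(t/60)^k) and H = −ln(1 − m), mean post-death days up to T are the integral of F from 0 to T. H is 0.799 for m = 0.55 and 0.528 for m = 0.41. The exponential case is k = 1; smaller k puts deaths earlier.

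| Window | k | 55% arm | 41% arm | Difference |
|---|---|---|---|---|
| D0–D28 | 1 | 4.63 | 3.18 | 1.4 |
| D0–D28 | 0.7 | 6.58 | 4.58 | 2.0 |
| D0–D28 | 0.5 | 8.37 | 5.90 | 2.5 |
| D0–D60 | 1 | 18.67 | 13.38 | 5.3 |
| D0–D60 | 0.7 | 21.62 | 15.57 | 6.1 |
| D0–D60 | 0.5 | 24.12 | 17.46 | 6.7 |

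The last column is how far the arm contrast moves between the literal and the alive-only definition.

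**Step 2: the scores with equal catheter use.** Exponential survival; catheter in place, or RRT continuing, for 7 days or until death in both arms.

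| Score (mean days) | 55% arm | 41% arm | Difference |
|---|---|---|---|
| Catheter-free to D28, literal | 21.3 | 21.2 | +0.1 |
| Catheter-free to D28, alive only | 16.7 | 18.0 | −1.3 |
| Last RRT to D60, literal | 53.3 | 53.2 | +0.1 |
| Last RRT to D60, alive only | 34.6 | 39.8 | −5.2 |

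Over catheter durations of 5 to 21 days, the literal catheter-free lead of the 55% arm is 0.05 to 0.85 days. Alive-only, that arm trails by 1.4 to 0.6 days. With equal use, the sign depends on the unstated rule.

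**Step 3: the scores with unequal catheter use.** Same model, early arm at 55% mortality with everyone catheterised, delayed arm at 41% with an assumed 50% or 60% ever catheterised.

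| Count | Early | Delayed, 60% | Delayed, 50% | Delayed advantage |
|---|---|---|---|---|
| Literal | 21.3 | 23.9 | 24.6 | 2.6 to 3.3 |
| Alive only | 16.7 | 20.7 | 21.4 | 4.1 to 4.7 |

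The lower-mortality arm scores better either way, but the literal count hides about 1.4 days, roughly a third, of its advantage.

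**The case against.** The strongest reply is that the article nowhere says that days after death count. Its endpoints are short labels, and catheter-free days can be read as alive and free. A fuller protocol or analysis plan, not shown, may give the rule. This stands as far as intent goes: the article does not show that post-death days will be counted. It does not remove the point, because the inconsistency lies in the wording that the article chose, within one list. It is weakest for the last-RRT interval, whose end is a fixed day.

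A reader might infer that the arm with more deaths will score better. The documents do not support that. The early arm is to have 100% RRT and the delayed arm RRT only when severity criteria occur. With a 7-day catheter and exponential survival, about 98% of delayed patients would need a catheter (6.68/6.79) before the literal scores were equal. That conflicts with the Discussion's premise that some delayed patients recover without RRT. Nor is the 1.4 to 2.5 days a lead for the higher-mortality arm: with equal 7-day use, the exponential model gives a lead of only 0.1 day.

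Two further limits stand. The article sets no direction of benefit for the last-RRT interval, so calling a long one a good score is an inference. That interval also has no value for patients who never receive RRT. Finally, survival at D28 is itself a secondary endpoint, so readers would see an imbalance in deaths.

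**Conclusion.** The point holds as a defect in two secondary endpoint definitions. Taken at their word, both credit time after death, more so in the arm with higher mortality, and both are out of line with the endpoints beside them. The arm contrast shifts by about 1.4 days within D28 (2.0 to 2.5 if deaths come earlier) and about 5.3 days within D60 (up to 6.7).

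These sizes rest on the planned mortalities applying at D60 and on the assumed survival shapes. The comparisons of full scores also rest on assumed catheter durations and shares. Which arm finally scores better cannot be settled from the article; what follows is that a real advantage of a lower-mortality arm would be understated. The correction should be made, but it does not touch the primary endpoint, the alpha levels or the sample size.

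**What to change.** - Redefine the first endpoint as *days alive without a dialysis catheter, D0 to D28*, with days after death counted as 0, in line with the three sibling endpoints.
- For the second, count only days alive after the last RRT up to D60, and state how patients never given RRT are scored. Rewording for death alone would leave that gap open.
- Make the change before any analysis of these endpoints by arm.

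The cost is a few phrases. Survival time from randomization is already collected for the primary endpoint, so no new data are needed. The one consequence is that the higher-mortality arm's scores become less favourable than under a literal count.
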